### Testing schedule

A detailed testing schedule of the trial protocol is depicted in Table 3.

**Table 3 Tab3:** Testing schedule of participants

Testing schedule	Task	Telephone screen	Face-to-face screen	Baseline(0 months)	Midpoint(3 months)	Endpoint(6 months)	Follow-up 4 weeks after endpoint(7 months)
Screening assessment	TICS-M	X					
	General medical history		X				
	MoCA		X				
	GDS		X				
	RAVLT		X				
CogState® battery	Identification task^a^			X	X	X	
	One card learning test^a^			X	X	X	
	Detection test^b^			X	X	X	
	One back test^b^			X	X	X	
CogState® additional test	Groton Maze learning test^b^			X	X	X	
Mood and fatigue outcome measures	DASS-42^b^			X	X	X	
	SHAI^b^			X	X	X	
	FACIT-F^b^			X	X	X	
Electrophysiological tasks	Word list immediate and delayed recall tasks^c^			X		X	
	Resting-state EEG^c^			X		X	
	Equiprobable Go/NoGo^c^			X		X	
Safety and compliance measures	FBC, E/LFT (bloods)^b^			X		X	
	Adverse effects^b^				X	X	X
	Compliance and blinding				X	X	X

^a^Co-primary outcome measures

^b^Secondary outcome measures

^c^EEG tasks will be completed by a subset of participants

*DASS-42* Depression, Anxiety, Stress Scale, *EEG* electroencephalography, *E/LFT* electrolyte and liver function test, *FACIT-F* Functional Assessment of Chronic Illness Therapy Fatigue Scale, *FBC* full blood count, *GDS* Geriatric Depression Scale, *MoCA* Montreal Cognitive Assessment, *RAVLT* Rey Auditory Verbal Learning Test, *SHAI* Short Health Anxiety Inventory, *TICS-M* modified telephone interview for cognitive status

### Study procedures and outcomes

A flow diagram of the participants for the proposed clinical trial is depicted in Fig. 1.

**Fig. 1 Fig1:**
[figure not shown]
Flow diagram of participants in the proposed clinical trial

### Screening

Telephone screening will be conducted with participants to determine their eligibility for the study. Participants will complete a modified version of the TICS-M, a validated screening tool for cognitive impairment [36], and will answer questions pertaining to the inclusion and exclusion criteria listed previously.

If successful, participants will be invited to attend the NICM Health Research Institute Clinical Research Laboratory and HEADBOX Laboratory at Western Sydney University for a face-to-face screening session. Participants will complete the GDS, Rey Auditory Verbal Learning Test (RAVLT), a general health questionnaire, and the MoCA.

### Cognitive functioning evaluation

Participants will complete a number of computerised and pen and paper cognitive tests during the trial. Table 3 lists the cognitive, mood, and fatigue measures that will be utilised in this study. Further detail of these measures are given below.

The CogState® pre-clinical Alzheimer’s Battery of tests will be utilised to measure baseline, 3-month and 6-month changes in cognition. In addition to the battery, the Groton Maze learning test (CogState® test) will be completed by participants. CogState® is a computerised cognitive test battery that has excellent test-retest reliability ranging from .76–.93 (intra-class correlation coefficient) [34]. Participants will complete a practice trial prior to the main trial, in accordance with previous literature [34, 37]. There are no known practice effects associated with completing the practice. Practice trials will help to provide a ‘true baseline’ measure as errors are generally made during the first instance of completing the task. Participants will become familiar with the tasks during the practice trials, and this will therefore ensure equity in the measurement of task outcomes between the testing timepoints. The CogState® battery will be administered at baseline (0 months), the midpoint (3 months), and the endpoint (6 months), again with no known practice effects between time intervals. Furthermore, this cognitive testing method enables investigation into multiple areas of cognition including processing speed, attention, short-term memory, working memory, and executive function. The co-primary outcomes (one card learning and identification tests) measure visual short-term memory and attention, while the secondary outcomes (Groton Maze learning test, detection, and one back tests) measure executive functioning, processing speed, and working memory, respectively.

The DASS is a 42-item self-report instrument designed to measure the three related negative emotional states of depression, anxiety, and stress. Participants who consistently score higher than the normal range for depression (0–9), anxiety (0–7), or stress (0–14) (during baseline and midpoint sessions) will be advised to speak to their general practitioner. There is an expectation that participants will score higher in each of the three domains compared with a population without SCI [4].

The SHAI is a shortened (18-item) measure of participants’ anxiety pertaining to their health. The highest total score is 52, indicating the highest level of health anxiety. Participants will complete the SHAI at baseline, the midpoint, and the endpoint. A comparison from baseline to endpoint will be made between treatment groups (active and placebo) to determine if health anxiety has decreased with the use of Cognition Support Formula® or placebo.

The FACIT-F is a self-report questionnaire utilised to determine a participant’s level of fatigue during their usual daily activities over the past 7 days. The FACIT-F is a 13-item questionnaire measuring the level of fatigue on a four-point Likert scale. The FACIT-F will be utilised to determine if fatigue and energy levels improve with the use of Cognition Support Formula®.

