**Method:**

One-hundred and twenty participants will be recruited for the randomised, double-blind, placebo-controlled study. Participants will be randomly assigned to one of the treatment groups (active or placebo) at a 1:1 ratio, and will be required to complete a series of cognitive (using CogState®), mood (using the Depression, Anxiety, Stress Scale (DASS-42) and Short Health Anxiety Inventory (SHAI)), and fatigue (using the Functional Assessment of Chronic Illness Therapy Fatigue Scale (FACIT-F)) tasks at baseline (0 months), the midpoint (3 months), and the endpoint (6 months). These tasks will be evaluated between timepoints (baseline vs. midpoint, midpoint vs. endpoint, and baseline vs. endpoint). Neurocognition will be measured by electroencephalography at baseline and at the endpoint in half of the participants. Adverse effects will be documented over the 6-month trial period.

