### Privacy and data management

In accordance with ethical guidelines, the anonymity, confidentiality, and privacy of participants will be protected. All electronic data will be password protected. Hardcopy source data records will be kept in a locked cabinet in the office of the principal investigator during data collection and at completion of the study for an indefinite period of time. All publication material will refer to general trial results as aggregate data and no individual participant names or identifying information will be released. Participants are welcome to view their personal data at any time during the trial.

As this is an investigator-led study with a small sample size, a data management committee and auditing process is not required. Quality control, decisions pertaining to amendments of the protocol, coordination of the trial, and development of the secure database and trial forms will be completed by the research team. Data will be stored within the secure REDCap system (version 8.5.7) and coded utilising IBM SPSS statistics software (version 23).

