### Randomisation, allocation concealment, compliance and adverse effects

Participants will be randomly allocated at a 1:1 ratio to either the treatment or placebo group using a permuted block allocation strategy. Computerised randomisation and allocation will be conducted using a unique random number generator in Microsoft Excel by a university staff member external to the research team. This external staff member sent the random sequence directly to the trial drug manufacturer, with participant IDs and unique batch codes to conceal the sequence. This is a double-blind trial, so both participants and the research team are blinded to treatment allocation until study completion. After eligibility is confirmed, participants will then be allocated to the next participant ID/numbered box of product by a member of the research team. Compliance will be assessed by advising participants to return any unused medication at the midpoint (3 months) and endpoint (6 months), and by completion of a diary by participants noting medication intake and adverse effects.

To monitor safety, participants will be referred to a local commercial laboratory (Laverty) prior to baseline and the endpoint testing sessions. Standard blood safety tests (full blood count, fasting blood glucose, liver and renal function tests) will be carried out. If participants receive an abnormal blood safety test result at baseline, they will not be enrolled in the study and will be encouraged to follow up their results with their regular health professional. Adverse events will be closely monitored throughout the course of the study.

In the case of a serious adverse event, and if the study drug is suspected as a potential cause and identifying treatment allocation is essential to the participant receiving appropriate medical care, unblinding of that participant only will occur. This will be done by the university staff member external to the research team who generated the computerised random sequence allocation.

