At the study midpoint, endpoint, and follow-up (7 months; 4 weeks after the endpoint) participants will be asked to which treatment condition they think that they have been allocated. Responses of Cognition Support Formula®, placebo, or unknown will be recorded. Responses will be checked against the condition allocated at the end of the trial after un-blinding. Participants who exit the trial early will also be contacted via telephone and asked to complete a trial exit interview pertaining to their experiences of the trial.

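### The DASS-42 GP-advice rule names baseline and midpoint only, so on its natural reading distress that starts on treatment and lasts to the endpoint prompts no advice

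*Protocol article*

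**What the plan says.** The Protocol article, under Cognitive functioning evaluation, sets a care rule for the DASS-42. It begins "Participants who consistently score higher than the normal range for depression" and gives the normal ranges as 0–9 for depression, 0–7 for anxiety and 0–14 for stress. It then names the sessions and the action: "during baseline and midpoint sessions) will be advised to speak to their general practitioner". The next sentence gives context: "There is an expectation that participants will score higher in each of the three domains compared with a population without SCI".

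The DASS-42 is collected at three sessions. The Abstract (Method) places the mood tasks "at baseline (0 months), the midpoint (3 months), and the endpoint (6 months". Table 3 (Testing schedule) marks the DASS-42 at the same three sessions in the block headed "Mood and fatigue outcome measures".

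Other provisions bear on participant care, but none is tied to a DASS-42 score:

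- **Adverse events** (Randomisation, allocation concealment, compliance and adverse effects): "Adverse events will be closely monitored throughout the course of the study".
- **Later contact** (same section): participants are asked to guess their allocation "At the study midpoint, endpoint, and follow-up (7 months; 4 weeks after the endpoint". Table 3 also schedules adverse effects and compliance at that 7-month contact.
- **Access to own data** (Privacy and data management): "Participants are welcome to view their personal data at any time during the trial".
- **Return of results** (Statistical analyses and dissemination): individual results go to participants who consent.
- **Screening** (Inclusion and exclusion criteria): a score above 19 on the 30-item Geriatric Depression Scale excludes. Table 3 shows this scale at the face-to-face screen only.

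**The concern.** The rule acts on persistence: one high score is not enough, but repeated high scores are. It then ties persistence to the first two of three sessions. The remaining pair of consecutive sessions, midpoint and endpoint, is also three months apart and shows persistence just as well, yet the sentence does not mention it.

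The participant affected is one who entered with normal scores, was raised at midpoint and was still raised at endpoint. This is distress that first appears after treatment starts. Safety and mood are both secondary aims of the trial, so this is an odd persistent pattern to leave out. Both scores are in hand by the endpoint visit.

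What is at stake is participant welfare on a small scale: whether someone with sustained raised scores is told to see a GP. Nothing inferential depends on it. The endpoint DASS-42 score does enter the efficacy analysis; only its use in the advice rule is missing.

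**Working it through.** The plan gives no figure to reproduce. The check applies the rule as worded to each possible pattern of scores and compares the results.

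**Inputs**

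- Sessions at which the DASS-42 is given: baseline (B), midpoint (M), endpoint (E), from the Abstract and Table 3.
- Sessions named in the rule: B and M, from Cognitive functioning evaluation.
- Condition: above the normal range, consistently, from the same sentence.

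**Readings compared**

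- Natural reading: raised at B **and** at M.
- Looser reading: raised at B **or** at M.
- Proposed rule: raised at B and M, **or** at M and E.

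For one subscale, each session is either raised or normal, so there are 2 × 2 × 2 = 8 patterns.

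| Raised at | Two consecutive sessions raised? | Natural reading | Looser reading | Proposed rule |
|---|---|---|---|---|
| none | no | no advice | no advice | no advice |
| B only | no | no advice | advice | no advice |
| M only | no | no advice | advice | no advice |
| E only | no | no advice | no advice | no advice |
| B, E | no | no advice | advice | no advice |
| B, M | yes | advice | advice | advice |
| M, E | yes | **no advice** | advice | advice |
| B, M, E | yes | advice | advice | advice |

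**Results**

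- Three patterns have two consecutive raised sessions: BM, ME and BME.
- Natural reading: covers BM and BME, 2 of 3. It misses ME.
- Looser reading: covers 3 of 3.
- Proposed rule: covers 3 of 3.

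**Which reading fits the text.** The looser reading would also send participants to their GP after a single raised score (B only, M only). That sits badly with the word *consistently* and with the joining of the two sessions by *and*. The natural reading is therefore the better one, but the sentence does not rule out the other, and two members of staff could apply it differently.

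**Is the gap closed elsewhere?** Adverse-event monitoring, the 7-month contact, access to one's own data and the return of results could each bring raised scores to light. None is linked to a DASS-42 threshold or to GP advice on that ground. The Geriatric Depression Scale exclusion works at entry only and cannot detect later elevation. No other place in the article sets GP advice on an endpoint DASS-42 score.

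**The case against.** The strongest reply is that nothing here is wrong. The article condenses a full protocol (version 6) that is not shown, and the handling of raised questionnaire scores may be set out there. The sentence promises advice to one group and does not say that others will go without. Collecting a score at three visits does not oblige anyone to have a referral rule at three visits. Baseline and midpoint are the sessions after which the participant is still in the treatment period, so a rule for care during the trial could sensibly stop there. After the endpoint, other routes remain. On the looser reading there is no gap at all. The two-consecutive-session yardstick is also the review's, not the plan's, and the proposed rule still leaves out the baseline-plus-endpoint and endpoint-only patterns.

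Much of this stands as a limit on the stakes. Other routes exist, advising others is not forbidden, the affected group is of unknown size and may be empty, and the full protocol may go further. Asking for repeated elevation is also reasonable at so low a threshold, given that higher scores are expected in this population; that part of the rule is not disputed.

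It does not remove the point. The article does not merely stay silent: it states a specific rule with thresholds, a persistence condition and named sessions. Followed as written on its natural reading, that rule treats two equally persistent patterns differently according to whether the elevation was present at entry. The two-consecutive-session yardstick is a fair extension of the rule's own demand for two raised sessions. If the looser reading was intended, the sentence still needs rewording. A 7-month contact is already scheduled, so the end of treatment is no practical bar.

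**Conclusion.** The concern holds, as a minor point worth considering. On its natural reading the GP-advice sentence covers 2 of the 3 patterns of sustained elevation on a subscale and misses the one in which a participant is normal at baseline and raised at both midpoint and endpoint. Participants raised at all three sessions are already covered.

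The conclusion rests on two assumptions: that *consistently* means raised at both named sessions, and that staff follow the published sentence rather than a fuller rule elsewhere. Under the either-session reading the gap disappears and only the ambiguity remains. The 2 of 3 is a count of patterns, not of people; the article gives no frequencies, so no risk can be estimated. The efficacy analysis, sample size and error rates are untouched.

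**What to change.** Reword the one sentence under Cognitive functioning evaluation along these lines:

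*A participant whose depression, anxiety or stress score exceeds the normal range at two consecutive DASS-42 sessions (baseline and midpoint, or midpoint and endpoint) will be advised to see a GP. Where the second raised score is at the endpoint, the advice will be given at that visit or at the 7-month contact.*

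This keeps the thresholds and the demand for persistence, and it settles which reading applies. Whether to act on a single raised endpoint score, and at what threshold, is a matter for the trial's clinicians.

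The cost is one sentence in the protocol. No assessment or visit is added, because the scores are already collected and the later contact exists. The downside is that a few more participants will be told to see their GP.

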### EEG protocol

EEG is an objective and non-invasive method of measuring neuronal activity. Utilisation of EEG in the proposed study will complement the cognitive measures previously outlined. Potential changes in participants’ resting EEG and task-related EEG from baseline to endpoint will be investigated. These changes include short- and long-term episodic memory encoding and retrieval, arousal, response activation, inhibition, and discrimination. Additionally, differences in the above-mentioned EEG methods between the treatment and placebo groups will be investigated.

### Statistical analyses and dissemination

For each participant in each group and at each timepoint the following data from the primary and secondary outcome measures will be assessed. For the CogState® detection, identification, one card learning, and one back tests, we will assess mean speed (ms), accuracy (%), and total number of hits, misses, and anticipations; for the Groton Maze test, we will assess the total number of errors; and for the mood (DASS-42, SHAI) and fatigue (FACIT-F) outcomes, we will assess subscale and composite scores. CogState® data that are not normally distributed will be transformed using logarithmic base 10 transformations. Generalised linear mixed models with a between-subject factor of group (treatment, placebo) and within-subject factor of time (baseline, midpoint, endpoint) will be conducted to assess differences in continuous co-primary and secondary outcome measures. Planned simple contrasts will be conducted to assess all timepoints (baseline vs. midpoint, midpoint vs. endpoint, and baseline vs. endpoint). To handle any missing data, analysis of last observation carried forward will be undertaken within the intention-to-treat analysis model. The premise of the intention-to-treat model includes all participants in the final analysis even if non-compliance, withdrawal, or deviation from the protocol occurs [38]. Due to the nature of drop-outs in clinical trials, this analysis will be carried out on all five primary and secondary outcome measures of cognition and secondary outcomes of mood (DASS and SHAI) and fatigue (FACIT-F).

All tests will be two-tailed, α = .05. MANOVAs and Pearson’s correlations may also be utilised for assessment of psychophysiological data depending on the outcome measures assessed. All data will be analysed using SPSS. Results from the trial will be presented publicly to the community through peer-reviewed journals and scientific conference presentations. Additionally, individual trial outcomes will be forwarded to participants, with their consent.

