## Abstract

**Background:**

Due to an ageing population in Australia there has been an increase in the number of older adults with subjective cognitive impairment (SCI), a self-reported decline in cognitive function associated with an increased risk of mild cognitive impairment and dementia. There is no current, recommended treatment for SCI; therefore, the effectiveness of a supplement approved by the Therapeutic Goods Association that has the potential to enhance cognitive function in an at-risk cohort should be tested. The primary aim of this proposed research is to determine the efficacy of 6 months of treatment with BioCeuticals Cognition Support Formula® (containing *Bacopa monniera* (brahmi), *Ginkgo biloba, Panax ginseng* and alpha-lipoic acid) on cognition in older adults with SCI (utilising the CogState® one card learning and identification tests as co-primary outcome measures of visual short-term memory and attention; mean speed (ms), accuracy (%), and total number of hits, misses, and anticipations) compared with placebo. The secondary aims are to assess an improvement in other cognitive domains (executive functioning, processing speed, and working memory), evaluate safety, adverse effects, and determine efficacy on mood, fatigue, and neurocognition. It is expected that improvements across the study timepoints in the co-primary outcomes in the active treatment group (compared with placebo) will be evident.

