In line with previous research examining individual constituents [1, 14, 16–25], we hypothesise that a 6-month dose of Cognition Support Formula® will improve cognitive functioning with minimal adverse effects in older adults with SCI compared with placebo. Due to limited literature in this area, exploratory analyses will be conducted in the domains of mood, fatigue, and neurocognition.

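### Each of the two co-primary tests carries five unranked metrics and three time contrasts, all at .05, so the primary comparison is not fixed and on most readings its false-positive risk exceeds 5%

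*Protocol article*

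**What the plan says.** Under Cognitive functioning evaluation, the protocol article names two co-primary tests: "The co-primary outcomes (one card learning and identification tests) measure visual short-term memory and attention". The abstract (Background) attaches metrics to them: "co-primary outcome measures of visual short-term memory and attention; mean speed (ms), accuracy (%), and total number of hits, misses, and anticipations". Statistical analyses and dissemination repeats the list for these tests, "we will assess mean speed (ms), accuracy (%), and total number of hits, misses, and anticipations", and gives no metric priority.

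The same section specifies the model, "Generalised linear mixed models with a between-subject factor of group (treatment, placebo) and within-subject factor of time (baseline, midpoint, endpoint", and then the comparisons: "Planned simple contrasts will be conducted to assess all timepoints (baseline vs. midpoint, midpoint vs. endpoint, and baseline vs. endpoint". It closes with "All tests will be two-tailed, α = .05".

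On timing, the abstract and Rationale and aims frame the primary aim as efficacy of six months of treatment. The abstract also states an expected result, which is improvement over the study's timepoints rather than at one of them. The sample size section works from a single CogState test and its group-by-time interaction. No section says whether success needs one co-primary test or both.

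**The concern.** Read literally, the co-primary outcome is 2 tests × 5 metrics, each examined at up to three contrasts, with every comparison held to its own .05. A favourable result on any one could be reported as a positive co-primary finding. A reader of the results could not then tell a pre-planned primary result from one selected among many. The power statement also covers one test, whereas the design has two.

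**Working it through.** **Inputs from the article.** Two co-primary tests, five metrics each, three contrasts, two-sided α = .05 per test. So 2 × 5 = 10 comparisons if only baseline versus endpoint counts, and 10 × 3 = 30 if any contrast counts.

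**Assumptions.** The article gives no correlations between metrics. They were varied from 0 to .95 within a test and from 0 to .9 between tests. The simple contrasts are taken as between-group differences in change, and visits as equally correlated.

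**Starting point.** One metric with one contrast gives the stated 5%. One metric with all three contrasts already gives about 12%.

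**Independence references.** 1 − .95^10 = .401 and 1 − .95^30 = .785. The second is only an upper reference: the baseline–endpoint change is the sum of the other two changes, so the 30 comparisons cannot be independent.

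**Simulation with that dependence kept.** For each metric, standardised group differences at three visits were generated under no effect (200,000 runs per setting) and the three change contrasts formed. The table shows the chance of a nominally significant primary result, in %.

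| Correlation within / between tests | Any of 10 (endpoint only) | Any of 30 | Favouring active, 10 | Favouring active, 30 | Both tests, endpoint | Both tests, any contrast |
|---|---|---|---|---|---|---|
| 0 / 0 | 40 | 73 | 22 | 49 | 5 | 23 |
| .5 / .3 | 32 | 61 | 16 | 36 | 5 | 18 |
| .5 / .5 | 29 | 57 | 14 | 33 | 8 | 22 |
| .7 / .7 | 21 | 44 | 11 | 25 | 8 | 21 |
| .8 / .5 | 21 | 45 | 11 | 26 | 4 | 12 |
| .95 / .9 | 11 | 25 | 6 | 14 | 6 | 14 |

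**One test null, the other truly effective.** If both must succeed and the effective test is sure to, the rule fails whenever the null test gives any nominal result. That chance is about 8–22% with the endpoint contrast only, and 20–48% with free choice of contrast.

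**Fewer distinct metrics.** If accuracy, hits and misses are counted as one, three metrics per test remain. The ranges become about 10–27% (endpoint only) and 23–54% (any contrast).

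**Power if both must succeed.** The stated 95% per test is taken as given. It cannot be confirmed, because the correlation between visits behind N = 100 is not stated. Joint power is .95 × .95 = .9025 if the tests are independent and about .912 at correlation .5, so about 90–91%.

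**Power at the first Holm step.** Take a 0.40 SD difference in change, N = 100 in two equal groups, and a visit correlation of .76 (the lower end of the article's reliability range, used as an assumption).
- SD of change = √(2 × (1 − .76)) = .693.
- Standardised difference = .40 / .693 = .577.
- Noncentrality = .577 × √(100/4) = 2.887.
- Power at .05: Φ(2.887 − 1.960) = .82.
- Power at .025: Φ(2.887 − 2.241) = .74.

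**The case against.** **The interaction may be the test.** The sample size rests on the group-by-time interaction, and one model is fitted per outcome before contrasts are listed. If the contrasts only describe that interaction, there are 10 primary tests, not 30. This is a fair reading and the reason to give the 10-test range first. However, the article does not make the contrasts conditional on the interaction, and ten unranked tests still give about 11–40%.

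**Six months is indicated.** The aim names that horizon, and the midpoint has a stated purpose, the stability of change over time. A reader might infer that no timepoint is indicated at all. The documents do not support that. They point towards the endpoint without fixing it, because the expected result is framed over all timepoints.

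**Co-primary often means both must succeed.** With the endpoint contrast, that reading brings the rate under no effect on either test to about 4–8%. It is not stated, though, and a null test paired with an effective one is still exposed to selection among metrics.

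**The analysis plan may settle it.** Adjustment methods and success rules are commonly left there, so the absence of a named procedure is not itself a fault. What stands is what the article positively sets: five metrics in the definition of the co-primary outcomes, three contrasts, and .05 throughout.

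**Related labels.** A reader might add that mood, fatigue and neurocognition are secondary aims in one paragraph and, in the next, "exploratory analyses will be conducted in the domains of mood, fatigue, and neurocognition". A secondary aim can be analysed in an exploratory way, and these outcomes do not change the error rate of the primary claim.

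**Conclusion.** The concern holds: the article does not fix one primary comparison for either co-primary test, and its stated rules allow selection among metrics and contrasts. Under no effect, the chance of a nominally significant primary result is about 11–40% for the endpoint comparison alone and 25–73% if any contrast counts. Counting only results that favour the active arm, these are about 6–22% and 14–49%. If both tests must succeed, the global-null rate is about 4–8% for the endpoint contrast and 12–23% with free choice of contrast.

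All of these ranges rest on assumed correlations. A reader might be tempted to quote 78.5% or the top of a range as the trial's actual error rate. The documents do not support that: the comparisons are dependent, the metric correlations are unknown, and the widest family is the least favourable of several possible readings.

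**What to change.** Before unblinding, amend the protocol and analysis plan as follows.

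- Name one metric for each co-primary test. The choice is the sponsor's, since nothing in the article favours a particular one.
- Name the between-group difference in change from baseline to month 6 as the single primary contrast.
- State the success rule. Either apply Holm to the two tests at an overall two-sided .05, or require both at .05 and restate power.
- Treat the remaining metrics and the other two contrasts as supportive.

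The change is to wording only and needs no new data. Under the assumptions shown, Holm lowers power at its first step from about 82% to about 74%. Requiring both tests gives about 90–91% joint power if each has 95%.
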